### Objectives

The overall objective of this study is to evaluate the efficacy, safety, and economic impact of 2 extended cytisinicline regimens (50 and 75 days duration) and compare them with the standard regimen (25 days).

The primary objective is to determine the efficacy of the maintained cytisinicline regimens (50 and 75 days) versus the standard 25-day regimen.

The secondary objectives are (1) to determine the percentage and number of adverse effects in each of the 3 treatment arms and (2) to analyze the economic impact of the maintained regimens versus the standard regimen in terms of cost-effectiveness and cost-utility.

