### Specific Outcomes Efficacy

Different outcomes will be used to measure the efficacy of cytisine in each arm of the clinical trial.

The sustained abstinence rate will be determined in each of the three treatment arms at 6 and 12 months, based on carbon monoxide co-oximetry results in ppm. The correlation between the sustained abstinence rate in each of the three arms studied at 6 and 12 months, based on co-oximetry results, and the self-reported abstinence at 6 and 12 months will be calculated.

Additionally, point abstinence will be analyzed every 7 days in each of the 3 arms studied, based on the results obtained in the CO tests.

The percentage increase in abstinence rates will be compared with the increase in the duration of cytisinicline use. The number needed to quit smoking for one patient in each treatment group will also be calculated.

Interval abstinence will also be determined in this clinical trial. The abstinence rate will be analyzed from Day 25 to Day 50 in all 3 study groups and from Day 25 to Day 75 in all 3 study arms. The abstinence rate will also be determined from Day 25 (usual arm), Day 50 (extended arm 1), and Day 75 (extended arm 2) up to 6 and 12 months.

Relapse rates will be analyzed in each treatment arm. The frequency and percentage of relapses will be determined in those who quit smoking from Day 25 (usual arm), Day 50 (extended arm 1), and Day 75 (extended arm 2) up to 6 and 12 months in all 3 arms.

Craving and withdrawal symptoms will be assessed during the clinical trial. The mean Minnesota Nicotine Withdrawal Scale (MNWS) score and the mean craving score will be calculated at the initial in-person visit in all 3 arms, and their change from this visit will be measured on days 25, 50, and 75 in all 3 study arms.

Predictors of continued abstinence at 6 and 12 months of treatment and of relapse (clinical, anthropometric, demographic, and smoking-related variables) will be determined in all study arms.

Quality of life in each group will be calculated using the EQ-5D-5L scale score at baseline, 50 days, 90 days, 6 months, and 1 year.

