### Statistical Analysis

#### Sample Size Determination

Based on clinical experience, it is estimated that the efficacy of cytisinicline prescribed in accordance with the data sheet is 30% (*P*^1^=.30), and that this efficacy will be greater if the maintenance regimen is extended over time. In this sense, it is hypothesized that the intermediate maintenance regimen could achieve an efficacy of 45% (*P*^2^=.40) and with the longest regimen, 50% sustained abstinence could be achieved (*P*^3^=.50). To obtain 80% power (pow=0.80) to detect differences at a 5% significance level (α=.05), 110 patients would need to be included in each arm. A loss rate of 21% is assumed, giving a final sample size of 402 patients (N=402).

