### Safety Analysis

The frequency and percentage of occurrence of adverse reactions shall be determined and categorized according to type/intensity. Calculate whether there are differences in each group compared to what is expected according to the product label.

To examine differences in the data between groups defined by the presence/absence of adverse events, the chi-square test will be applied for qualitative variables and the *t* test or the Mann-Whitney *U* test for quantitative variables. Finally, the causal relationship between safety, defined by the absence of adverse events, and treatment prolongation will be verified using multivariate logistic regression. To determine candidate variables, those with a statistical significance of *P*<.20 will be tested and included in a multivariate model.

All analyses will be performed with the statistical package SPSS (version 19.0; IBM Corp), and statistically significant values will be considered those whose *P* value is <.05.

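### A P<.05 rule for every analysis does not hold 5% across the two primary comparisons that share the 25-day control: the overall two-sided error is about 9%

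*Protocol article*

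**What the plan says.** The significance rule comes at the end of Safety Analysis, in a sentence that covers all analyses and not only safety: "statistically significant values will be considered those whose *P* value is <.05".

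Objectives puts two comparisons under one primary aim: "The primary objective is to determine the efficacy of the maintained cytisinicline regimens (50 and 75 days) versus the standard 25-day regimen". Trial Design states a single purpose, to show that maintenance therapy is superior to the standard regimen, with 1:1:1 allocation.

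The time point is less settled. Specific Outcomes Efficacy says "The sustained abstinence rate will be determined in each of the three treatment arms at 6 and 12 months", without ranking the two, and the Abstract also lists both. The list of efficacy variables in Textbox 2 gives continuous abstinence at six months only. Efficacy Analysis describes one dichotomous efficacy variable for the main objective, to be derived by an algorithm written after data collection.

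Sample Size Determination aims for 80% power "to detect differences at a 5% significance level". It assumes 30% abstinence on 25 days, 45% (or .40, in the bracket) on 50 days and 50% on 75 days, and arrives at 110 per arm and 402 in total. Nowhere does the article state an adjustment, a testing order, a global test used as a gate, or a division of alpha.

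**The concern.** The objection is to a stated rule, not to a missing detail. Applied as written, the rule gives each extended arm its own full 5% chance of producing a significant result. Both results feed one claim about one drug at different durations, and either could be presented as proof that longer treatment works. The error rate attached to that claim is therefore the chance that at least one of the two tests is falsely significant, which exceeds 5%. A positive report on one arm alone would carry weaker evidence than its P value suggests.

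**Working it through.** **Inputs from the article.** Threshold .05 for every test (Safety Analysis; the same alpha in Sample Size Determination). Sidedness is not stated; two-sided is assumed. Allocation 1:1:1. Two comparisons under the primary objective. Abstinence 30%, 45% or 40%, and 50%. 110 per arm.

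**1. Which test does the stated sample size match?**

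- Global three-arm chi-square (2 df) at .05, noncentrality λ = n Σ(pᵢ − p̄)² / [p̄(1 − p̄)]. With 30/45/50%: p̄ = .4167, Σ(pᵢ − p̄)² = .02167, p̄(1 − p̄) = .2431. At n = 110, λ = 9.81 and power is 80.7%; the smallest n for 80% is 109. With 30/40/50% it is 116.
- Pairwise 30% versus 50% at .025, unpooled: n = (2.241 + 0.842)² × (.21 + .25) / .20² = 109.3, so 110. The pooled version gives 113.
- Pairwise at .05: 30% versus 50% needs 93 (103 with continuity correction); 30% versus 45% needs 163.
- Total: 110 × 1.21 = 133.1, rounded up to 134, and 3 × 134 = 402.

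So 110 fits either a global test or a halved alpha, and does not fit unadjusted pairwise tests. The article does not say which was used.

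**2. Error with two comparisons at one time point.** With equal arms, each difference has variance 2σ²/n and the two share the control's σ²/n, so their correlation is (σ²/n) / (2σ²/n) = 0.5. Then

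1 − P(|Z₁| < 1.96 and |Z₂| < 1.96; ρ = 0.5) = 9.1%.

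For scale, independent tests would give 1 − .95² = 9.75%, and the upper bound is 2 × 5% = 10%. Counting only results that favour longer treatment gives about 4.5%, against a nominal 2.5%.

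**3. If both time points were also primary.** There would be four tests, with correlation 0.5 between comparisons and an assumed r between times (multivariate normal simulation, 2 million draws):

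| r between 6 and 12 months | Two-sided chance of at least one P<.05 |
|---|---|
| 0.9 | 12.6% |
| 0.8 | 13.9% |
| 0.7 | 14.9% |
| 0.5 | 16.2% |

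The extremes are 9.1% at r = 1 and 17.3% at r = 0. The article gives no value for r. Sustained abstinence at 12 months is nested in that at 6 months, so r = √[p₁₂(1 − p₆) / (p₆(1 − p₁₂))]. An assumed fall from 30% to 20% gives √(.14/.24) = 0.76 and an error of about 14.3%; a fall to 25% gives √(.175/.225) = 0.88 and about 13%.

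**4. Power with 110 per arm.** Dunnett's critical value for two comparisons is 2.212, a per-test level of about .027.

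| Comparison | Unadjusted .05 | Dunnett |
|---|---|---|
| 30% vs 50% | 86.2% | 79.8% |
| 30% vs 45% | 63.4% | 53.5% |
| 30% vs 40% | 34.2% | 25.4% |

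**The case against.** The strongest reply is that the article does not say that two separate 5% tests decide the trial. The Abstract speaks of differences among the three groups, and 110 per arm agrees with a global three-arm test or an alpha of .025. With three arms, a global 5% test that must succeed before pairwise 5% tests does hold 5% at one time point. It can be added that the threshold sentence is generic, follows the software statement, and that multiplicity detail often sits in an analysis plan, which is not shown here.

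Part of this stands. The sample size may have been built on a controlled procedure. But no gate or split is stated anywhere, while a threshold for all analyses is. A reader following the text would apply .05 to each comparison.

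A reader might also infer a stronger point: that any of four tests, two comparisons at two times, can establish superiority, so that the false-claim rate is about 15%. The text does not support that as a finding. Efficacy Analysis refers to a single efficacy variable, Textbox 2 lists six months only, and no section makes 6 and 12 months co-primary. That figure also rests on an assumed correlation. Nor should 9.1% be read as the chance of wrongly declaring longer treatment better: it counts both directions, and the favourable half is about 4.5%.

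**Conclusion.** The point holds in limited form. With P<.05 applied to each of the two primary comparisons at a single time point, the two-sided chance of at least one false significant result is about 9.1% instead of 5%; for false superiority of longer treatment it is about 4.5% instead of 2.5%. This rests on equal arm sizes, two-sided tests, the large-sample normal approximation, and no unstated gate.

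The range of about 13% to 16% is conditional on 6 and 12 months both being treated as primary and on an assumed correlation of 0.9 to 0.5. The article leaves the primary time point open, so the range shows what that ambiguity could cost; it is not the error rate of the plan as written. The matter should be corrected, and can be without changing the size of the trial.

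**What to change.** Before any outcome data are seen, state the following:

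- Six months, already listed in Textbox 2, is the single primary time point for sustained abstinence; 12 months is secondary.
- 75 versus 25 days is tested first at two-sided 5%. 50 versus 25 days is tested at two-sided 5% only if the first is significant.
- Confirmatory use of P<.05 is limited to this sequence; other P values are descriptive.

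This takes a few sentences and no added patients. The first test keeps its full alpha, with about 86% power for 30% versus 50% at 110 per arm. The price is that the 50-day regimen cannot be claimed superior if the first test fails. That deserves thought, because the Abstract itself warns that the longest regimen may threaten adherence.

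If the sponsor does not want one comparison to depend on the other, Holm or Dunnett would serve. These cost power: under Dunnett with 110 per arm, from about 86% to 80% for 30% versus 50%, and from 63% to 54% for 30% versus 45%. If a global test was intended as a gate, as the sample size would allow, saying so would also hold 5% at one time point.

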### Economic Impact Analysis

For the economic impact analysis, direct costs (medical and nonmedical) and indirect costs will be included.

Health outcomes will be quantified in terms of quality-adjusted life years in our economic evaluation. The health-related quality of life index (utilities) for these outcomes has been estimated using the EQ-5D-3L data for smokers and ex-smokers from the 2017 National Health Survey.

Effectiveness results will be quantified in terms of years of life lost prematurely compared to the average life expectancy for men and women.

The cost-utility analysis of administering cytisinicline at the standard regimen versus 2 sustained cytisinicline therapies will be performed using the incremental cost-utility ratio. This will be calculated as the incremental cost in Euro per additional unit of quality of life gained by one alternative compared to the other. Cost differences between the 2 alternatives/differences in quality-adjusted life years between the 2 alternatives

The cost-effectiveness analysis of administering cytisinicline at the standard regimen versus 2 cytisinicline-based therapies will be performed using the incremental cost-effectiveness ratio. This will be calculated as the incremental cost in Euro per life-year gained for one alternative compared to the other.

Differences in costs and life-years lost between the 2 alternatives will be estimated. All results will be presented for different time horizons, including the short-time (5 years), medium-time (10 years), and long-time (20 years).

To assess the uncertainty of the results, univariate and multivariate deterministic sensitivity analyses will be conducted under the following assumptions: the first scenario, univariate deterministic sensitivity analysis, will consider reducing only the efficacy rate of cytisinicline by 50% while maintaining the discount rate at 3% as in the baseline analysis. The second scenario, multivariate deterministic sensitivity analysis, will consider reducing the efficacy rate by 50% but increasing the discount rate to 6%.

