**Methods:**

A prospective, multicenter, open-label, controlled, parallel, phase IV clinical trial of 402 smoker patients prepared to quit smoking. The study was conducted in 10 hospitals in Spain. A control group is compared to 2 intervention groups in which the duration of the drug is increased without increasing its dose, administering half and all, respectively, of an additional marketed container that includes 100 tablets. Thus, participants will be randomized to three groups in a 1:1:1 ratio to receive cytisinicline: (1) a control group treated with cytisinicline according to the usual clinical guidelines and product information (25 days); (2) a group with a 50-day cytisinicline regimen (an additional 25 days at a dose of 1.5 mg every 12 hours), seeking to increase its efficacy while minimally impacting adherence; and (3) a group with a 75-day regimen (an additional 50 days at a dose of 1.5 mg every 12 hours), attempting to increase its efficacy, although the longer duration of the drug may threaten adherence. Efficacy in the 3 arms will be analyzed through sustained abstinence at 6 and 12 months, point abstinence rate assessed every 7 days, and abstinence rate from Day 25 to Day 50 and from Day 25 to Day 75 in the 3 study arms. (1) The variation in withdrawal and craving symptoms in the 3 groups, (2) safety through the percentage of adverse events in the 3 treatment arms, and (3) economic impact by evaluating the cost-effectiveness and cost-utility ratios of the 2 prolonged regimens versus the usual clinical cytisinicline regimen. To calculate the differences between the 3 groups for each outcome variable, a univariate analysis will be performed. Statistically significant variables will be included in a multivariate model.

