### Specific Outcomes (Economic Evaluation)

The economic analysis of 2 prolonged cytisinicline regimens vs a standard regimen will be performed by calculating their cost-effectiveness and cost-utility ratios. The effect of treatment adherence on the cost-effectiveness and cost-utility ratios of the considered therapeutic alternatives will also be evaluated.

The effect of the different predictors of sustained abstinence at 6 and 12 months (clinical, anthropometric, and demographic variables) will be evaluated in relation to cost-effectiveness and cost-utility in the three arms of the clinical trial.

The future effects (15, 30, and 50 years after smoking cessation) will be simulated in each of the treatment arms.

Finally, a budget impact model will be constructed to analyze the potential savings for the National Health System for each of the 3 therapeutic options proposed in this clinical trial.

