This is a low-intervention study due to several characteristics: (1) studies of extended regimens exist in the European Union [23]. These analyze the efficacy and safety of extended cytisinicline treatments of 40 and 84 days. We also have experience with extended doses of 1.5 mg every 12 hours for 3 months [24]; (2) modifications to drug administration are minimal. One of the study arms corresponds to the regimen used in daily clinical practice; and (3) patient selection was performed according to the drug’s prescribing information. All of this ensures its feasibility.

Unlike other studies that propose a substantial change in the dose and frequency of the molecule, this one uses extended treatment regimens of an additional 25 and 50 days, with minimal modification to the commercially available drug formulation. Thus, in Spain, each pack of cytisinicline contains 100 tablets, so one-third of patients will be randomized to take half the tablets contained in the additional pack (2 tablets a day for an additional 25 days) and another third to take all of them in that pack (2 tablets a day for an additional 50 days). Furthermore, these regimens, with their lower administration frequency, could be more adherent than regimens of 3 times a day for 12 weeks.

At the time of this writing in Europe, the same dose and duration of cytisine are used for all smokers. However, smokers represent a heterogeneous patient population with differences in dependence, emotionality, motivation, and comorbidities. This study, using a multivariate model, allows the identification of the group of patients who would require extended treatment with cytisinicline, personalizing its use in routine practice.

It is a multicenter study conducted in different geographical areas of Spain, with a representative sample. Moreover, it is carried out by a research group with experience in the diagnosis and treatment of smoking cessation. Patients treated in 10 specialized smoking cessation units accredited by scientific societies are included. Furthermore, this is an independent trial, free from the financial interests of the pharmaceutical industry, which enhances the rigor of the results. Funding for disseminating the results will be obtained through grants or public funds.

This trial incorporates the calculation of the economic impact of extended doses, determining the savings for the National Health System that these regimens could generate by increasing the number of ex-smokers.

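### The planned cost-effectiveness and cost-utility ratios compare each extended regimen only with 25 days, so the value of going from 50 to 75 days is not planned to be shown

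*Protocol article*

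**What the plan says.** Four places in the protocol article set the economic comparison, and all use the 25-day regimen as the reference.

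- Abstract, Methods: "economic impact by evaluating the cost-effectiveness and cost-utility ratios of the 2 prolonged regimens versus the usual clinical cytisinicline regimen".
- Objectives (secondary objective 2): "to analyze the economic impact of the maintained regimens versus the standard regimen in terms of cost-effectiveness and cost-utility".
- Specific Outcomes (Economic Evaluation), in its opening sentence: "The economic analysis of 2 prolonged cytisinicline regimens vs a standard regimen will be performed by calculating their cost-effectiveness and cost-utility ratios".
- Economic Impact Analysis: "The cost-utility analysis of administering cytisinicline at the standard regimen versus 2 sustained cytisinicline therapies will be performed using the incremental cost-utility ratio", and in parallel "The cost-effectiveness analysis of administering cytisinicline at the standard regimen versus 2 cytisinicline-based therapies will be performed using the incremental cost-effectiveness ratio".

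The Economic Impact Analysis section then defines the ratio for a pair of options: "This will be calculated as the incremental cost in Euro per life-year gained for one alternative compared to the other". It does not order the three regimens, does not mention dominance, and does not name a comparison of 75 with 50 days. The only economic item that covers all three options together is the budget impact model in the economic outcomes. That model estimates savings and is not an incremental ratio.

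**The concern.** A patient or a health service can adopt only one of the three durations. In that setting, the question about the longest regimen is what its additional 25 days buy beyond the 50-day regimen. The ratio of 75 against 25 days does not answer it, because it pools the first extension with the second. If the first extension is efficient and the second is not, the pooled figure can look acceptable while the second step is poor value. The reverse can also happen: a 50-day regimen that is dominated would still be reported with a ratio of its own. The economic evaluation is a stated secondary objective, and the protocol expects it to inform National Health System spending.

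**Working it through.** The document states no cost-effectiveness ratio and no prices, so there is no figure of the plan's own to reproduce. The check uses extra tablets as the cost unit and extra quitters as the effect unit.

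**Inputs**
- Efficacy (Sample Size Determination): 30% for 25 days and 50% for 75 days. For 50 days the text gives 45% and the bracket beside it gives .40. Both are carried through.
- Extra tablets (Trial Design; Discussion, Principal Findings): 2 × 25 = 50 for the 50-day arm and 2 × 50 = 100 for the 75-day arm. The Discussion describes these as half and all of one additional pack: "each pack of cytisinicline contains 100 tablets, so one-third of patients will be randomized to take half the tablets contained in the additional pack".

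**Formula:** ratio = difference in extra tablets ÷ difference in quit rate.

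| Case | 50 vs 25 days | 75 vs 25 days | 75 vs 50 days (not planned) |
|---|---|---|---|
| 45%, tablets taken | 50/0.15 = 333 | 100/0.20 = 500 | 50/0.05 = 1000 |
| .40, tablets taken | 50/0.10 = 500 | 100/0.20 = 500 | 50/0.10 = 500 |
| 45%, whole pack charged to both arms (assumption) | 100/0.15 = 667 | 100/0.20 = 500 | 0/0.05 = 0 |
| .40, whole pack charged to both arms (assumption) | 100/0.10 = 1000 | 100/0.20 = 500 | 0/0.10 = 0 |

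**Reading the table**
- In the first row, 500 is the weighted mean of the two steps: (0.15 × 333 + 0.05 × 1000)/0.20 = (50 + 50)/0.20 = 500. The step from 50 to 75 days costs twice the pooled figure.
- In the second row the three ratios coincide and nothing is hidden. This is the boundary case. On tablets taken, a 50-day efficacy below 40% makes the first step dearer than the second, and the 50-day regimen is then extendedly dominated.
- In the last two rows the 50-day arm has the same drug cost as the 75-day arm and a lower quit rate, so on drug cost alone it is dominated. The planned ratio against 25 days would not show this.

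**Savings per quitter.** Suppose each extra quitter saves the equivalent of S tablets (assumption; the document gives no figure). In the first-row case, net cost relative to 25 days is 50 − 0.15S for 50 days and 100 − 0.20S for 75 days.
- For S between 500 and 1000, both extended regimens save money against 25 days, so both planned ratios are negative. The 75-day regimen still costs more than the 50-day one. At S = 600 the net costs are −40 and −20, so 75 versus 50 days costs 20/0.05 = 400 per extra quitter.
- For S above 1000, the 75-day regimen is both cheaper and more effective than the other two.

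**The case against.** The strongest reply is that the stated aim is extended regimens against standard care. No objective asks for a choice between 50 and 75 days, and ratios against usual care answer the question as worded. The point has some force. Even so, the economic section evaluates three options side by side with a view to health-service use, and reporting two ratios against a common reference invites readers to compare them.

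A second reply is that this is a condensed article. Dominance checks and costing rules are commonly left to a health-economic plan, which is not shown. That stands for the costing of the half-used pack, which is not part of this point. It does not remove the point about the comparator, which the document states in four places.

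A third reply is that drug cost per quitter is not the plan's ratio. The plan uses life-years and QALYs, direct and indirect costs, discounting and several time horizons. This stands too. The factor of 2 belongs to the illustration and need not carry over. Savings per quitter change the numerators, and if they are large enough the 75-day regimen dominates and the planned comparator misleads nobody.

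A reader might also infer that the 75-versus-50-day ratio will never be computed. The document does not support that. Its definition of the ratio is generic about which two alternatives are compared, and a fuller economic plan may exist. What can be said is that this document does not plan it.

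**Conclusion.** The point holds as a gap in the specified comparison. As written, the plan gives two ratios against 25 days, no ratio for 75 against 50 days, and no step to identify a dominated regimen. With three mutually exclusive options, that can mislead about the last 25 days of treatment.

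The size is not fixed. On drug quantity alone, with 30%, 45% and 50%, the step from 50 to 75 days costs 1000 tablets per extra quitter against a pooled 500. The distortion is nil with the bracketed .40 and runs the other way if a whole pack is charged to both arms. A reader might infer that the plan understates the cost of the last 25 days by half, or that one duration is already shown to be poor value. Neither follows, because the figures leave out prices, other costs, savings, life-years and QALYs.

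The matter concerns a secondary objective and does not touch the primary efficacy comparison or data collection. It is worth correcting before results are known, so that the economic comparator is not chosen afterwards.

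**What to change.** In Economic Impact Analysis, amend the sentence that introduces the cost-utility ratio and the parallel sentence for the cost-effectiveness ratio to specify a full incremental analysis:

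1. Order the three regimens by total cost.
2. Remove any regimen that is dominated (no cheaper and no more effective than another, and worse on at least one of the two) or extendedly dominated (its ratio is higher than that of the next more effective regimen).
3. Report each remaining ratio against the next less costly regimen that has not been removed, including 75 versus 50 days where neither has been removed.

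Keep the ratios against the 25-day regimen as supplementary results, since they answer the objective as stated. Adjust the wording that refers to two alternatives so that it fits three.

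The cost is a few lines of text and one further ratio from arm-level costs and effects that the plan already needs. No new data or visits are required. The small downside is that one regimen may be reported as dominated.
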